#### *7.2.1.2 FGD, IDI, and Structured Observation Data*

To contextualize our survey findings, we will conduct a qualitative analysis involving FGD and IDI transcripts and research memos from structured observations. Specifically, we will search for patterns in the data that help: 1) explain the efficacy, fidelity, and efficiency of CFL models and the SOC; 2) describe the various capabilities of CFL providers and the systems in which they operate; and 3) define the most salient “core elements” of each CFL model and 4) establish distinguishing and common features for each CFL model.

To identify major and minor themes that explain those patterns, we will analyse FGD transcripts and structured observation memos using content analysis methodology and appropriate analytical software (i.e. NVivo, Atlas TI, Dedoose, etc.). The process of eliciting themes will involve: a) familiarization through careful reading of FGD transcripts and research memos, noting emergent themes; b) performing open coding in which codes are created based on identified themes, codes are assigned to specific sections of transcripts, and double-coding is conducted on a sample of data to promote inter-coder reliability; c) developing a codebook; d) performing data reduction in which an inventory is taken of what is related to the given code, capturing the variation or richness of each theme and noting differences between individuals or among subgroups; e) data display using matrices and tables; and, f) interpretation in which we search for relationships among themes or concepts identified and develop diagrams in order to map out relationships in the data. Particular attention will be paid to the rationale for how themes are grouped, and to the types of messages grouped together. Two investigators, one of which will include the principal investigator, will review all qualitative data, independently identify emergent themes, and confer to agree upon final coding and findings.

For all qualitative analyses, we will apply established qualitative research methods including principles of triangulation, negative case analysis, and respondent validation. Triangulation, a powerful tool to cross-validate qualitative research findings, refers to comparing results from multiple sources (in this case, results of structured observations and focus group discussions, in addition to the findings of in-depth interviews from Objective 2 below) to identify patterns of data convergence or divergence across the models being studied. Negative case analysis involves the identification of experiences that appear to contradict the theoretical assumptions underpinning the study (i.e. that CFL models promote MIP retention and engagement in the PMTCT continuum) and generates rival explanations. Respondent

validation and peer debriefing allow for the review and confirmation of preliminary descriptions and findings with research participants. The aforementioned methods will be used in combination to ensure that our qualitative findings are internally valid and that our conclusions are robust.

## **7.2.2 Analysis Plan for Objective 2 & 2a**

### **7.2.2.1 Cohort Data**

We will calculate maternal retention in care as the proportion of mothers alive and in care at 6, 12, and 24 months post-ART initiation among all eligible women at the start of the cohort. We will also calculate median days from PMTCT enrolment to ART start to examine the effects of CFL models on time to ART initiation. We will look for differences in the delay of ART initiation across the CFL models and SOC using the Aalen-Johansen estimator to account for the competing event of death. We will report crude HEI mortality at 12 and 24 months as part of our survival analysis. We will define infant 12-month HIV free survival as the proportion of HEIs alive with a negative 12-month HIV-rapid test among all infants enrolled in the HEI birth cohort. Similarly, we will define infant 24-month HIV free survival as the proportion of HEIs alive with a negative 24-month HIV-rapid test among all infants enrolled in the HEI birth cohort. We will use Kaplan Meier techniques to compare infant HIV-free survival at 12 and 24 months across the 3 CFL models and SOC accounting for informative censoring and differences in baseline patient characteristics between the models using inverse probability weights. We will censor all survival outcomes on the last date of field activities in a given district (most likely between February 1, 2018 and April 30, 2019, depending on the district), the date of transfer, or the date of the last clinical encounter, as appropriate.

We will explore associations between CFL model and individual-level maternal care retention and infant HIV-free survival at 12 and 24 months using multivariate log binomial regression modelling. We will estimate the effect of receiving any CFL service on the risk of 12-month maternal LTFU and viral suppression, controlling for other measured individual- and catchment area-level covariates, including age, pregnancy number, district, facility type, and number of women registered in the PMTCT cohort, among others; we will conduct a sub-group analysis for women who initiated ART while breastfeeding. We will repeat this analysis to examine effects of CFL model components—including client-to-provider ratio, frequency of provider-client interaction, pro-active versus reactive visit adherence approach, presence of CFL provider remuneration, CFL provider training frequency and duration, availability of one-on-one psychosocial support, and other variables—on maternal 12-month LTFU, maternal viral

suppression, and infant 12- and 24-month HIV-free survival. For maternal viral suppression, we will use survival analysis methods to control for variability in the timing of outcome ascertainment and to enable comparison of viral suppression between groups accounting for interval censoring. For the 24-month HIV-free survival outcome, we will control for infants who do not reach 24 months of age by the time of outcome ascertainment by excluding them from the analysis (so that the outcomes for all infants are represented by those who made it to 24 months in the study). As a check on the robustness of this approach, we will conduct a sensitivity analysis and use inverse probability weighting of those with outcomes at 24 months (compared to the total study sample) to account for any potential differences between infants who have and do not have a 24-month outcome at the time of field outcome ascertainment. Risk differences, unadjusted risk ratios, and adjusted risk ratios with accompanying 95% confidence intervals will be estimated for each model. Of note, these estimates will include the MIPs lost to routine care who are traced through the study, therefore allowing for more robust estimates of true outcomes in the study cohort.

All estimates will be corrected based on the outcomes of sampled MIPs using methods established for general HIV programs. The weights for outcomes of interest will be derived from the product of the inverse probability of sampling for the facility catchment area ( $1/[0.25]$ ), and the inverse probability of sampling for the MIP (between  $1/[80/100]$  and  $1/[10/100]$  depending on the final enumeration cohort), and the inverse probability of participation given that a MIP was sampled ( $1/[P(R = 1 | W = w)]$ ).

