## 6.0 Methodology

### 6.1 Study Design Overview

We propose to rigorously define and compare three widely adopted models for community-facility linkage with each other and the standard of care using a mixed methods approach involving both quantitative and qualitative data collection.

For the quantitative component, we will first use stratified random sampling to select facility catchment areas in 5 Malawi districts where implementing partners have focused PMTCT programming. We will then visit each selected area to construct a retrospective cohort of HIV-infected women who entered the national PMTCT program and received CFL services or the SOC between July 1, 2016 and June 30, 2017. These dates have been chosen to align with the latest change to Malawi HIV guidelines supporting universal “test and treat” strategy, which became national policy on April 1, 2016 and reached stable rolled out on July 1, 2016. Using existing data, we will gather individual-level retrospective data on each woman and her infant from PMTCT enrolment through the child’s second birthday. Next, we will enrich these data using an epidemiological sampling method designed to overcome the limitations traditionally associated with retrospective data (e.g. missing data, outcome misclassification, etc.). In this second stage, we will randomly select a sample of women from our full

cohort to create our nested cohort. These women will complete a questionnaire about their experiences with CFL models and services, undergo viral load testing, and have their children ages 12–24 months receive HIV testing. Such prospective data collection will enable us to confirm primary outcomes, fill in missing data, and improve study data quality more generally.

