## **6.5.2 Study Procedures for Objectives 2 & 2a**

### **6.5.2.1 Objectives 2 & 2a Overview**

In “real-world” PMTCT programmatic settings where the absolute numbers of MIPs is large, prospectively ascertaining clinical outcomes, including maternal viral load and infant/young child HIV status, is often challenging for an implementation research study such as this one. Therefore, we will learn about MIP health outcomes using an efficient, two-stage cohort design.

In the first stage, we will retrospectively construct a cohort of HIV-infected women entering the national PMTCT program and receiving community-facility linkage (CFL) services or the SOC between July 1, 2016 and June 30, 2017 in our 40 randomly selected facility catchment areas. For all areas, we will review existing, routine MOH data for all eligible women and their infants to abstract retrospective data on our outcomes of interest—12-month maternal retention in care, viral suppression for HIV-positive mothers, and 12-month infant HIV-free survival. (Of note, maternal and infant outcomes have two different “starting points” for determining the 12-month outcome, which we will account for in our analysis—in the case of HIV-positive mothers the “starting point” is ART initiation date and for infants it is date of birth).

In the second stage, we will use epidemiological sampling to obtain outcomes on a nested cohort of approximately 1,200 randomly selected MIPs drawn from the full retrospective cohort (*see section 6.4 Sample Size*). Information will be collected from these 1,200 participating MIPs through a detailed questionnaire and blood sampling for maternal viral load and infant HIV testing, and will be enriched by qualitative in-depth interview (IDI) data for 60 women purposively selected from among the MIPs in the nested cohort. IDIs will explore maternal perceptions, experiences, and satisfaction with CFL models and services, including with their key components, and how these services have affected their longitudinal engagement with and retention in the national ART program.

Data from the first and second stages will be combined to present the HIV care cascade for MIPs in aggregate, and by CFL model/ SOC, from HIV testing through ART initiation and viral suppression. Uptake of HIV services at the three main steps of the HIV care cascade will be calculated according to UNAIDS definitions and compared against established “90-90-90” benchmarks (*see section 7.2.2.2 below*).

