#### **6.5.2.2 First Stage Data Collection: Chart Review**

In the first stage of data collection, we will seek out outcome information for all MIPs in the full retrospective cohort by abstracting existing clinical and demographic data from routine MOH treatment cards and registers and from electronic medical records (where available) at our 40 selected facility catchment areas. Study staff will have no direct contact with MIPs in the retrospective cohort, apart from those MIPs selected to potentially participate in the nested cohort.

Information to be abstracted will include such data as: HIV testing history, 6-, 12-, and 24-month post-ART initiation maternal vital status (e.g. alive in care, transferred out, stopped ART, died, and lost to follow-up); 6- and 24-month maternal viral load (timing per national guidelines); exposed-infant first HIV-1 DNA PCR result (from 6 weeks of age per national guidelines); 12- and 24-month HEI vital status (including death); and 12- and 24-month HEI HIV sero-status (timing per national guidelines). We will also abstract the first documented DNA PCR test result for all HEIs from HCC registers and treatment cards and laboratory records, which will include results for samples taken at 6 weeks of age and later, including “late” test results for HEIs who enrolled into follow-up after 6 weeks of age. Similarly, many HIV-exposed children undergo their 12- and 24-month rapid tests after these time points due to late presentation to clinic for “milestone” visits, HIV test kit stock outs, and other reasons. As a result, the “median age at first HIV rapid testing” may be closer to 15 or 18 months than the recommended 12 months, providing valuable information about HEI HIV status at or near the conclusion of breastfeeding. Because HEIs enrolling into routine HIV care through June 30, 2017 are eligible to join the full retrospective cohort, some HEIs will not reach age 24 months before administrative censoring (anticipated to take place between end 2017 and end 2018, depending on the district). The 12-month calendar period for cohort construction was selected to maximize power for the primary outcome (i.e. 12-month maternal HIV retention in care). 24-month outcomes for infants who are censored before reaching age 24 months will be represented by those who are observed at age 24 months and by a simple sensitivity analysis (*see section 7.0 Data Analysis*).

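### Maternal retention keeps all eligible women in the denominator, although some cannot be observed at 24 months (or, in early-closing districts, 12) and the closing dates conflict

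*Protocol*

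**What the plan says.** Protocol section 6.1 builds the cohort from women who "entered the national PMTCT program and received CFL services or the SOC between July 1, 2016 and June 30, 2017". Section 6.5.2.1 sets the clock: "in the case of HIV-positive mothers the “starting point” is ART initiation date and for infants it is date of birth". Section 7.2.2.1 states: "We will calculate maternal retention in care as the proportion of mothers alive and in care at 6, 12, and 24 months post-ART initiation". The same sentence fixes the denominator: "at 6, 12, and 24 months post-ART initiation among all eligible women at the start of the cohort". It then relates care model to "individual-level maternal care retention and infant HIV-free survival at 12 and 24 months using multivariate log binomial regression modelling". Section 7.1 names 12-month maternal retention as the primary outcome.

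Two places say when observation ends. Section 6.5.2.2 gives administrative censoring as "anticipated to take place between end 2017 and end 2018, depending on the district". Section 7.2.2.1 says "We will censor all survival outcomes on the last date of field activities in a given district", and dates this as "most likely between February 1, 2018 and April 30, 2019, depending on the district".

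For subjects who have not reached a time point there is one rule, in section 7.2.2.1. Infants who are not yet 24 months old at ascertainment are left out of the 24-month analysis, with an inverse-probability-weighted sensitivity check. There is no counterpart for mothers at 12 or 24 months.

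**The concern.** A woman who starts ART on 30 June 2017 reaches 12 months at the end of June 2018 and 24 months at the end of June 2019. The second date is later than any closing date in the protocol. The first is later than the early part of both windows. Under the literal definition such a woman stays in the denominator but cannot enter the numerator.

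Nothing else in the text removes the problem. The censoring sentence is about survival outcomes, whereas maternal retention is a proportion analysed by log binomial regression, which does not handle censoring. The weights in section 7.2.2.1 cover selection of the site, selection of the pair and participation, not insufficient follow-up time.

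At stake are the level of retention reported for each model and the absolute and unadjusted comparisons between models. Closing dates differ by district, and care model is tied to district. In the illustrative Table 1, Salima and Neno contain only CHW sites.

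**Working it through.** **Inputs.** Entry window 1 July 2016 to 30 June 2017, 365 days (section 6.1). Time origin is ART start (section 6.5.2.1). Closing dates come from sections 6.5.2.2 and 7.2.2.1. Retention of 73% under SOC, an 8-point effect, and 298 SOC and 894 CFL mothers come from section 6.4. Two assumptions are not in the protocol: entry is even over the window, and ART starts at entry.

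**The plan's own figure first.** For 73% vs 81%, two-sided alpha 0.05, 80% power and 3:1 allocation, the pooled proportion is (0.73 + 3 × 0.81)/4 = 0.79. The SOC sample size without continuity correction is

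[1.96·√(4/3 × 0.79 × 0.21) + 0.842·√(0.73 × 0.27 + 0.81 × 0.19/3)]² / 0.08² ≈ 281.1, so 282.

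With the continuity correction it is 298, so 894 CFL, exactly as stated. The sample size is not in dispute.

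**Share able to reach month m.** Share = (days from 1 July 2016 to [close minus m months], both days counted) / 365, limited to the range 0 to 1.

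| District close | Reach 12 months | Miss 12 | Reach 24 months | Miss 24 |
|---|---|---|---|---|
| 31 Dec 2017 | 184/365 = 50.4% | 49.6% | 0% | 100% |
| 1 Feb 2018 | 216/365 = 59.2% | 40.8% | 0% | 100% |
| 30 Jun 2018 | 100% | 0% | 0% | 100% |
| 31 Dec 2018 | 100% | 0% | 184/365 = 50.4% | 49.6% |
| 30 Apr 2019 | 100% | 0% | 304/365 = 83.3% | 16.7% |

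Under the same assumptions the 6-month time point is reached by everyone, even with a close on 31 December 2017.

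**Effect of the literal definition at 12 months.** If retention does not depend on entry date, recorded retention = true retention × share able to reach 12 months.

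- Close 1 Feb 2018: 0.73 × 0.592 = 43.2% and 0.81 × 0.592 = 47.9%. The gap falls from 8 to 4.7 points. The ratio stays at 0.73/0.81 = 0.90.
- Close 31 Dec 2017: 0.73 × 0.504 = 36.8% and 0.81 × 0.504 = 40.8%. The gap is 4.0 points and the ratio again 0.90.
- Unequal closing: two groups with the same true 73%, one closing on 1 February 2018 and one after 30 June 2018, would show 43.2% and 73% in an unadjusted comparison.

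**Cost of restricting to women who can be observed.** If every site closed on 1 February 2018, about 298 × 0.592 = 176 SOC and 894 × 0.592 = 529 CFL women would remain. Power for 73% vs 81% would be about 61%, against 82.2% for 298 and 894 by the same formula (no continuity correction; 80.1% with it). If every site closed on 31 December 2017, about 150 and 451 would remain, with power about 55%. These are worst cases, because closing differs by district.

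**The case against.** The strongest reply is that the protocol never says how an unobserved month-12 or month-24 status is coded. It gives a numerator and a denominator only. The statuses to be abstracted in section 6.5.2.2 do not include a category for follow-up that ended too soon, and a woman still attending when her district closes does not meet the programme's definition of lost to follow-up. For the 12-month LTFU outcome in section 7.2.2.1 she would not be a failure. This stands in part: scoring her as not retained follows from the stated proportion and is not an explicit instruction. But the LTFU reading does not solve the problem. It would count her as not lost after less than 12 months at risk, which errs the other way.

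Three further points limit the concern.

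- The 12-month problem is conditional. A close on or after 30 June 2018 lets every woman who started ART by 30 June 2017 reach 12 months. Much of both windows satisfies this, the dates are forecasts, and no district is assigned an early one. A reader might infer that the primary outcome is incomplete throughout the study; the protocol does not support that.
- A reader might also infer that the care-model effect is confounded with closing date. Section 7.2.2.1 lists district as a covariate, and a common observable share cancels from a within-district ratio, as shown above. The adjusted ratio is therefore much less exposed than risk differences, unadjusted ratios and descriptive proportions. The districts with only CHW sites appear in a table labelled illustrative.
- Maternal retention at 24 months is not among the outcomes in section 7.1. It appears only in the analysis text, and the protocol gives no expected value for it, so a projected 24-month percentage would rest on an invented figure.

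It can also be said that the two windows overlap and come from different contexts, chart review and the end of field work. However, section 7.2.2.1 makes the last field date the censoring date, so both describe when observation stops, and they differ at both ends.

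**Conclusion.** The point holds in a limited form. Without any assumption, the two closing windows contradict each other. Nor, with a denominator of all eligible women, can maternal retention be observed at 24 months for those who start ART late in the entry window, at any stated close. For the primary 12-month outcome the same is true only in districts that close before 30 June 2018, which both windows allow.

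The sizes are endpoint cases: about 50% or 41% miss 12 months at the two earliest closes, and between 17% and 100% miss 24 months. They rest on even entry and ART start at entry. Women already on ART would reach the time points sooner, and women starting after entry would reach them later. The distortion falls on descriptive proportions, absolute differences and unadjusted comparisons, and less on the district-adjusted ratio.

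**What to change.** 1. Replace the two date ranges with one consistent statement of closing date by district.
2. For each maternal time point, restrict the denominator to women whose ART start is at least that long before their district's close. This extends the infant exclusion rule and its inverse-probability-weighted check to mothers. Alternatively, estimate retention by a time-to-event method with administrative censoring at the district's close.
3. Where feasible, order chart abstraction across districts so that 12-month status is taken no earlier than 12 months after the last eligible ART start.

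The first two changes are wording; the third affects only the order of field work. The price is that the 24-month estimate, and the 12-month estimate in any early-closing district, rests on fewer women. The third step removes the 12-month loss where it can be done.

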#### **Secondary Outcomes:**

- Proportion of pregnant women newly registered in ANC who received HIV testing services
- Proportion of HIV-infected PMTCT clients initiated on anti-retroviral therapy
- 6-month post-ART initiation retention in care for HIV-positive mothers
- Proportion of HIV-positive mothers achieving HIV virological suppression from 6 months post-ART initiation (at MOH-recommended times of 6 and 24 months post-ART and, through the study, at time points between 12 and 24 months post-ART initiation)
- 12-month infant HIV-free survival
- Exposed infant “early” HIV infection status (i.e. HIV-1/2 DNA PCR result) from age 6 weeks
- 24-month child HIV-free survival
- 12- and 24-month infant HIV sero-status
- Median time from PMTCT enrolment to maternal ART initiation
- Median age of ART initiation for HIV-infected infants and young children
- Proportion of HIV-infected infants and young children achieving HIV virological suppression (from 6 months post-ART initiation per MOH guidelines)

- Proportion of HIV-infected mothers and infants who “returned to care” within 30 and 60 days of meeting the national ART program definition of loss to follow-up/ “defaulting” (i.e. not known to have transferred out, stopped or died AND have not returned to the clinic for 2 months after the woman is expected to have run out of ARVs).
- Proportion of HEIs who “returned to care” within 30 and 60 days of meeting the national HIV Care Clinic (HCC) programme definition of loss to follow-up/ “defaulting” (i.e. not known to have transferred out, stopped or died AND have not returned to the clinic for 2 months after the “next appointment date” given at the last HCC visit).

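### No confounder adjustment is stated for the comparison of delay to ART initiation across CFL models and SOC, which leaves it open to confounding by district

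*Protocol*

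**What the plan says.** Time from PMTCT enrolment to ART start is a listed secondary outcome in Protocol section 7.1: "Median time from PMTCT enrolment to maternal ART initiation". Section 7.2.2.1 gives its purpose as calculating "median days from PMTCT enrolment to ART start to examine the effects of CFL models on time to ART initiation", and its between-model method as "We will look for differences in the delay of ART initiation across the CFL models and SOC using the Aalen-Johansen estimator". The stated reason for that estimator is "using the Aalen-Johansen estimator to account for the competing event of death". Nothing else is attached to this analysis.

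Other analyses in the same section carry adjustment:

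- The Kaplan-Meier comparison of infant HIV-free survival is made "accounting for informative censoring and differences in baseline patient characteristics between the models using inverse probability weights".
- The regressions for the effect of any CFL service on 12-month maternal loss to follow-up and viral suppression control for individual and catchment-area covariates, "including age, pregnancy number, district, facility type, and number of women registered in the PMTCT cohort, among others". The same analysis is repeated for model components, with infant HIV-free survival added.

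Time to ART is not among the regression outcomes. The correction that closes section 7.2.2.1 and applies to all estimates is a product of site-sampling, pair-sampling and participation weights.

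**The concern.** The study is observational (section 6.5.2.3.7), so a woman's model depends on where she was seen. Section 6.2 describes districts that range from largely rural to one with an urban centre, and ART start could differ between them whatever the model. Table 1 shows the models unevenly distributed over districts. A comparison that deals only with competing death would mix the district difference with the model difference.

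The sampling and participation weights do not help. They make the nested sample represent the full cohort, but they do not make the models comparable with one another.

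At stake is one secondary outcome whose result would be read as an effect of the CFL models when part of it may be district mix.

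**Working it through.** The protocol states no figure for this comparison, so there is none to reproduce. The check asks how far district mix alone could move the crude contrast.

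**Which counts apply.** PMTCT/ART enrolment and ART start dates are abstracted for the whole retrospective cohort (sections 6.5.2.2 and 6.6.3). The relevant district shares are therefore those of all available mothers, not of the roughly 30 sampled per site. Table 3 gives ranges of available mothers per stratum, and the midpoints are used here.

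| Model | Lilongwe | Mzimba | Zomba | Salima | Neno | Total |
|---|---|---|---|---|---|---|
| SOC | 90 | 105 | 80 | 0 | 0 | 275 |
| Mentor mother | 450 | 150 | 175 | 0 | 0 | 775 |
| Expert client | 175 | 350 | 1,000 | 0 | 0 | 1,525 |
| CHW | 80 | 0 | 150 | 350 | 75 | 655 |

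The totals add to 3,230, the midpoint of Table 3's overall range of 2,740 to 3,720.

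**Zomba shares.**
- Expert client: 1,000/1,525 = 0.656
- Mentor mother: 175/775 = 0.226
- SOC: 80/275 = 0.291

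**Formula.** Suppose the models have no effect. Cumulative ART initiation by a given day is p in Lilongwe and Mzimba and p + d in Zomba. The crude figure for model m is then p + s_m·d, where s_m is its Zomba share. The spurious difference between models a and b is (s_a − s_b)·d.

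- Expert client vs mentor mother: (0.656 − 0.226)d = 0.43d
- Expert client vs SOC: (0.656 − 0.291)d = 0.36d (0.3648 unrounded)

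For an assumed d of 10 to 20 points, the shifts are about 4.3 to 8.6 points and 3.6 to 7.3 points.

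**Sensitivity to the ranges.**
- All lower ends: 900/1,350 = 0.667, 150/650 = 0.231 and 60/230 = 0.261, giving 0.44d and 0.41d.
- All upper ends: 1,100/1,700 = 0.647, 200/900 = 0.222 and 100/320 = 0.313, giving 0.42d and 0.33d.
- Nested-sample counts (180/330, 60/300 and 60/180): (0.545 − 0.200)d = 0.35d and (0.545 − 0.333)d = 0.21d.

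**CHW.** Salima and Neno supply 350 + 75 = 425 of 655 CHW mothers (65%), or 270 of 390 (69%) by nested-sample counts. Neither district has an SOC, mentor-mother or expert-client site. If those two districts differ from the rest by e points, the crude CHW vs SOC contrast shifts by 0.65e, or 6.5 points at an assumed e of 10. Weighting cannot balance district for these women. District overlap between CHW and SOC exists only in Lilongwe and Zomba, with 80 + 150 = 230 CHW mothers and 90 + 80 = 170 SOC mothers at the midpoints.

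**The case against.** The strongest reply is that silence is not a decision. The section never calls this comparison unadjusted, an Aalen-Johansen estimator can carry weights, and covariates for one secondary outcome are often left to an SAP, which is not at hand. The listed outcome is a median, and the objectives mention control of confounding only under 2a. Much of this stands. A reader might infer that the protocol rules out adjustment, or that the result is confounded. The text supports neither: it supports only that no adjustment is stated and that the contrast is open to confounding. What the reply does not remove is that the protocol itself picks the estimator, says what it corrects for, words the aim as an effect, and in the same paragraph names baseline differences between models as something to handle for another outcome.

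Two further inferences would go too far:

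- A reader might take the Kaplan-Meier weights to include district. They name baseline patient characteristics, and district is named only in the regression covariate list.
- A reader might take time to ART to be the one unadjusted comparison among adjusted ones. The covariate list is tied to any CFL service and to components, while the by-model regression is only called multivariate. The cascade indicators in section 7.2.2.2, maternal ART initiation among them, are compared across models with no stated adjustment.

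It is also fair that a single d for Zomba treats Lilongwe and Mzimba as alike, which section 6.2 makes doubtful.

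**Conclusion.** The point holds as a limited one. For a secondary outcome described as an effect of the CFL models, the protocol states an estimator that handles competing death and states no handling of confounding, in a non-randomised comparison where model and district are linked by design. District mix alone would shift the crude contrasts by about 0.43d (expert client vs mentor mother) and 0.36d (expert client vs SOC).

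These factors rest on Table 3's illustrative midpoints, on one common difference between Zomba and the other two districts, and on no true model effect. The protocol gives neither d nor its sign, so the actual size and direction of any bias cannot be derived. A reader might carry the concern over to the primary outcome. The documents do not support that, because the 12-month maternal loss-to-follow-up analysis has stated covariates including district.

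**What to change.** In section 7.2.2.1, state that cumulative incidence of ART initiation will be compared across models and SOC with an inverse-probability-weighted Aalen-Johansen estimator. Build the weights from the covariates already named for the regressions (age, pregnancy number, facility type, district), plus pregnant or breastfeeding status at entry, which the eligibility criteria in section 6.3 already require. Show the crude curves alongside.

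For CHW vs SOC, make the district-adjusted comparison within Lilongwe and Zomba. Report the Salima and Neno CHW results descriptively, and state that they cannot be adjusted for district.

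The change is a few sentences and needs little new data, since weighting for model differences is already planned for infant HIV-free survival. The costs are somewhat wider intervals and a smaller CHW group in the adjusted contrast: about 230 of 655 mothers at the Table 3 midpoints. Table 3 expects only two SOC sites in each of three districts, so weights using district and facility type together may meet empty cells. Overlap should be checked and reported.
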